#### Safety analysis

For each reactogenicity type, the presence of any post-vaccination reactogenicity, aggregated over all injections, will be summarized and compared between the treatment groups using Fisher’s exact test.

The numbers and percentages of participants experiencing AEs will be summarized by body system and preferred terms within a body system using the MedDRA dictionary. Summaries of AEs will also be generated by drug relationship and intensity. The maximum intensity and/or relationship for an AE within a patient will be used in these summaries. As appropriate, proportions of participants experiencing specific adverse events will be compared between the study treatments by Fisher’s exact test.

#### Immunogenicity analysis

Summary statistics including geometric mean concentration and corresponding 95% confidence interval, mean, minimum, maximum, 25^th^ and 75^th^ percentiles, standard deviation, and standard deviation in the log scale of antibody concentrations will be calculated for each time point. The immunogenicity data will be summarized on the ITT Analysis Set only.

#### Withdrawal symptoms analysis

We use baseline MNWS scores as the average of the scores over the screening and Day 0 visits. Follow-up MNWS scores for each participant will be averaged over non-missing weekly MNWS scores during each collection period (from 1–4 weeks during each collection period). Change from baseline on the average MNWS scores during each collection period will be analyzed with weighted analysis of covariance (weighted ANCOVA) models which will include the treatment group and center as factors and corresponding baseline MNWS score as a covariate. The number of non-missing weekly MNWS scores during each collection period (between 1 and 4 per participant) will be used as the weight. In addition, weekly MNWS scores collected throughout the study will be analyzed using mixed-effects repeated measures models. The overall treatment effect will be presented, along with the associated 95% confidence interval and p-value.

#### Nicotine dependency analysis

The baseline score is defined as the average of the scores collected during the screening and at week −2. A participant is considered as a smoker for completion of the FTND when smoking at the time of data collection, or if the participant has smoked cigarettes during the previous 7 days. Change from baseline in FTND at week 24 and 52 will be analyzed with similar ANCOVA (unweighted) and mixed-effects repeated measures models as described for the MNWS scores. The repeated measures analysis comparing NicVAX^®^ and placebo will be conducted for participants who are still smoking at the time of Fagerström data collection.

#### Cigarette consumption analysis

Baseline cigarette consumption is defined as the average of the screening visit and week −2.

A mixed-effects repeated measures analysis using the change from baseline data will be provided. The overall treatment effect will be presented, along with the associated 95% confidence interval and p-value. Change from baseline to week 24 and week 52, for those participants still smoking during week 26 and week 52 respectively, will be analyzed using ANCOVA, as described previously. The week 52 analysis will use the last available week’s data for completers who due to visit scheduling do not have week 52 data (e.g. week 51).

### Handling drop outs and missing data

Participants who withdraw from the study will be considered smokers for the remainder of the study. In the absence of CO measurement during a planned clinical visit, the confirmation on smoking status will be imputed using the CO measurements of both bordering visits. An abstinent status will only be assigned when both bordering visits are no more than one planned clinical visit apart and both CO measurements at these visits are < 10 ppm (i.e., participants are not allowed to miss two consecutive visits with CO measurements). In all other cases, a smoking status will be assigned. The refusal by a participant to undergo CO testing during a clinic visit will be considered to be an elevated CO level and the participant to be a smoker.

Any missing self-reports on smoking status will be imputed using both of the bordering non-missing weekly self reports. A missing self-report will be assigned an abstinent status only when both bordering self-reports have abstinent status. This imputation will only be carried out if the two bordering self-reports are no more than 4 weeks apart.

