### Primary outcome measure

Our primary efficacy outcome for this study is defined as biochemically validated prolonged abstinence from week 9 to 52, measured by the participants’ self-reported smoking consumption on a weekly base and confirmed by exhaled carbon monoxide (CO) measurements in weeks 10, 12, 14, 18, 24, 28, 34, 40, 46, and 52, in the absence of use of NRTs during this entire period. If a CO measurement has been collected, it should confirm the smoking status of the participant for that week. A participant is considered to be a validated non-smoker with a CO level <10 ppm measured by a MicroCO (Micro Medical ltd., United Kingdom). When a participant is a self-reported non-smoker with an elevated CO level of ≥10 ppm, the CO-measurement supersedes the participants’ self-report and the participant is defined as a smoker.

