#### Abstinence from week 37–52

A secondary efficacy variable for this study is the biochemically confirmed 16-week abstinence at 12 months from weeks 37 to 52. This measurement is defined as the proportion of participants who maintained abstinence from weeks 37 to 52 measured by the weekly self-reports on smoking consumption, confirmed by exhaled CO measured at week 40, 46, and 52, and who also do not use NRTs during this period.

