#### Lapse and relapse rate from week 12–52

Among participants with 4-week abstinence status at 12 weeks, we define relapse as at least 2 consecutive weekly self-reports that are positive for tobacco use. A lapse is defined as 1 weekly self-report for tobacco use followed and preceded by 1 weekly self-report for tobacco abstinence.

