## Appendix A. Secondary objectives

• To evaluate safety and immunogenicity,

• To evaluate long term abstinence from week 37–52,

• A bstinence from week 9–52 and week 37–52 in the subset of NicVAX subjects with the high antibody responses,

• To evaluate four week abstinence from week 9–12,

• To evaluate abstinence from week 37–52 for subjects who were intolerant to varenicline or who were non-abstinent from week 9–12,

• To evaluate point prevalence (7-day abstinence; PP) at 12, 26 and 52 weeks,

• To evaluate relapse rate post week 12 among subjects with 4-week Abstinence status at 12 week. Relapse is defined as at least 2 consecutive weekly diary entries for tobacco use.

• To evaluate abstinence from week 9–24.

• To evaluate time to first Relapse among subjects with 4-week Abstinence status at 12 week,

• To evaluate time to first Lapse among subjects with 4-week Abstinence status at 12 week. Lapse is defined as 1 weekly diary entry for tobacco use followed and preceded by 1 weekly diary entry for tobacco abstinence,

• To evaluate time between first Lapse and first Relapse among subjects with 4-week Abstinence status at 12 week,

• To evaluate withdrawal symptoms using Minnesota Nicotine Withdrawal Scale, measured at screening and during weeks 12–15, weeks 26–29, and weeks 49–52.

• Nicotine dependency measured by the Fagerström Test for Nicotine Dependence.

• To evaluate Cigarette consumption.

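### For participants with missing week-12 data, entry to the relapse and lapse analyses depends on week 13–14 data that are already outcome time

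*Protocol article*

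**What the plan says.** In the protocol article, Handling drop outs and missing data, a missing CO test is handled from both sides: "the confirmation on smoking status will be imputed using the CO measurements of both bordering visits". Abstinence is granted only if both neighbouring values are below 10 ppm and no two CO visits in a row were missed. The rule is then closed: "In all other cases, a smoking status will be assigned". Self-reports follow the same two-sided logic: "A missing self-report will be assigned an abstinent status only when both bordering self-reports have abstinent status", with a limit of 4 weeks between the two reports. No exception is made for a visit at the edge of an endpoint's window.

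Under Primary outcome measure, abstinence is "confirmed by exhaled carbon monoxide (CO) measurements in weeks 10, 12, 14, 18, 24, 28, 34, 40, 46, and 52". Table 1 agrees, and shows weeks 11 and 13 as telephone contacts without CO.

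Lapse and relapse rate from week 12–52 restricts the analysis: "Among participants with 4-week abstinence status at 12 weeks". It defines relapse by two or more successive weekly reports of smoking. Appendix A uses the same restriction for the time-to-event endpoints, for example "To evaluate time to first Relapse among subjects with 4-week Abstinence status at 12 week", and gives weeks 9–12 as the window for four-week abstinence.

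**The concern.** A cohort for a relapse analysis should be fixed by what is known when follow-up starts. Here follow-up starts at week 12, but for anyone without week-12 data the rule waits for week 13 or 14 before deciding whether that person had quit. Someone abstinent in weeks 9–11 who misses the week-12 CO, then smokes and shows a raised CO at week 14, is scored as a smoker at week 12. That person is not counted as a relapse but drops out of the denominator as never having quit.

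The interval matters. Varenicline ends at week 12, the point at which the article expects antibody levels to start protecting against relapse, and the Discussion presents the trial as a relapse prevention study. At stake are the relapse rate, the times to first relapse and first lapse, and the time between the two.

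**Working it through.** **Context figure.** The stated sample size reproduces and is not in dispute. For 22% against 34%, two-sided 5% and 90% power, n = [1.960·√(2·0.28·0.72) + 1.282·√(0.22·0.78 + 0.34·0.66)]² / 0.12² gives 293 per arm. With 300 per arm the power is 90.7%.

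**Step 1: which data decide week 12.** CO visits around week 12 are weeks 10, 12 and 14 (Primary outcome measure; Table 1). A missing week-12 CO therefore has neighbours 10 and 14. A missing week-12 report has neighbours 11 and 13, as reports are weekly. Relapse and lapse are assessed over weeks 12–52 (Secondary objectives), so weeks 13 and 14 are outcome time.

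**Step 2: enumerate the cases.** Hold fixed: week-12 CO missing, week-10 CO below 10 ppm, reports for weeks 9–11 abstinent. Assume the week-12 status needs CO confirmation. Vary the week-12 report (abstinent or missing), the week-13 and week-14 reports (abstinent or smoking) and the week-14 CO (<10, ≥10 or missing). That is 2 × 2 × 2 × 3 = 24 patterns. Entry requires week-14 CO <10 ppm and, if the week-12 report is missing, an abstinent week-13 report.

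Six patterns are relapses in weeks 13–14 (both reports positive):

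| Week-12 report | Week-14 CO | Result |
|---|---|---|
| Abstinent | <10 | enters |
| Abstinent | ≥10 | excluded |
| Abstinent | missing | excluded |
| Missing | <10 | excluded |
| Missing | ≥10 | excluded |
| Missing | missing | excluded |

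Five of the six are excluded. Of the 18 patterns without a relapse in those weeks, 5 enter and 13 are excluded: 12 because the week-14 CO is ≥10 or missing, and 1 because the week-12 report is missing and week 13 is a lapse. The patterns are not equally likely; the count shows only what the rule does.

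**Step 3: size.** The article expects about 45% abstinence in weeks 9–12, so 0.45 × 300 = 135 quitters per arm. Early relapsers removed = 135 × (proportion missing week 12) × (proportion of quitters relapsing in weeks 13–14). Neither proportion is in the article, so both are assumed:

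- 5% and 10%: 135 × 0.05 × 0.10 = 0.7
- 5% and 20%, or 10% and 10%: 1.35
- 10% and 20%: 135 × 0.10 × 0.20 = 2.7

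These are upper values for the assumed rates, because they treat every such relapser as excluded.

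**Step 4: effect on a rate.** As a rough stand-in for relapse in the placebo arm, take the fall from 45% to 22%: 135 − 66 = 69 of 135, or 51.1%. If only relapsers are removed, (69 − r)/(135 − r) is 50.9% for r = 0.7, 50.6% for r = 1.35 and 50.1% for r = 2.7.

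**Step 5: direction.** If s non-relapsers are removed as well, the rate is (69 − r)/(135 − r − s). It stays at 51.1% when s = r × 66/69 = 0.96r. For r = 2.7 that is s = 2.6: 66.3/129.7 = 51.1%. A larger s would raise the rate.

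**Step 6: between arms.** Use 1 − 22/45 = 51.1% and 1 − 34/45 = 24.4%, a difference of 26.67 points, with 135 quitters in each arm. Over a wider assumed range (2–20% missing week 12; 10–40% of relapses falling in weeks 13–14; only relapsers removed), 0.1 to 5.5 placebo and 0.1 to 2.6 NicVAX relapsers are removed. The difference becomes 26.65 to 26.09 points, a change of at most about 0.6 points.

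**The case against.** Several objections carry weight.

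- *The gate is not relapse itself.* Relapse is defined by self-report, while a missing week-12 CO is resolved by the week-14 CO. Report forms are completed weekly regardless of clinic attendance, and the inclusion criteria admit smokers from 8 ppm, so a relapser with a completed week-12 report and a week-14 CO below 10 ppm is possible and enters. This stands. A reader might infer that those who missed week 12 enter only if they do not relapse in weeks 13–14; the rule does not say that.
- *Non-relapsers are excluded too.* This stands, and by step 5 it can cancel or reverse the shift. A reader might infer that relapse must be understated and a vaccine benefit shrunk. The documents do not establish either.
- *The 69 are not relapses.* Correct. Loss of week 9–52 abstinence also arises from a single smoking week, a raised CO, use of nicotine replacement, withdrawal or data that cannot be imputed. The 51.1% serves only to show scale.
- *CO confirmation is not stated for the week-12 status.* Also correct, though the missing-data section is written generally. If the status rests on self-report alone, the CO route disappears, but a missing week-12 report followed by smoking in week 13 still excludes the participant.
- *Edge handling belongs in the full protocol or analysis plan.* This would answer an omission. The article instead states a complete rule with a default for all other cases, and that rule produces the problem.

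**Conclusion.** The point holds as a minor flaw in a stated rule: with missing week-12 data, entry to the relapse and lapse analyses depends on data from after entry. The likely size is about 0 to 3 relapsers per arm, given assumed rates of 5–10% missing week 12 and 10–20% early relapse, with about 135 quitters per arm. The net direction is uncertain.

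The week-12 case does not touch the primary endpoint: week 14 lies inside weeks 9–52, so smoking then is a failure anyway. The rule does reach outside other windows. A missing week-10 CO looks back to week 8; week 24 looks ahead to week 28; and week 40 looks back to week 34, although weeks 37–52 abstinence is "confirmed by exhaled CO measured at week 40, 46, and 52". A reader might infer that the whole imputation scheme should be confined to in-window data. That does not follow. No size has been estimated for these cases. Moreover, week 52 has no later visit, so confirming a missing last CO from one side would newly count some participants as abstinent on the primary endpoint, against the plan's choice to treat missing as smoking.

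**What to change.** Add one sentence to Handling drop outs and missing data: as the entry condition for the relapse and lapse analyses, 4-week abstinence status at week 12 is set only from CO tests and self-reports up to week 12. One workable form for a missing week-12 CO is week-10 CO below 10 ppm plus abstinent self-reports for weeks 9–12, and otherwise not abstinent. Leave the present conservative rule in place for week 52 and for the primary endpoint.

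No new data are needed. The cost is that a participant with a missing week-12 CO is either confirmed from one side only, since weeks 9–12 contain just two CO tests, or left out of the relapse cohort. Under either choice, what happens in weeks 13 and 14 no longer decides who is analysed.

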## Discussion

This will be the first study to evaluate the efficacy of a nicotine conjugate vaccine, NicVAX^®^, combined with varenicline as an aid in smoking cessation and relapse prevention. In addition, this is also the first trial to combine nicotine vaccination with an evidence-based smoking cessation pharmacotherapy. Although NicVAX^®^ is primarily designed as a smoking cessation aid, rather than a pharmacotherapy to prevent relapse in smokers who already quit, nicotine vaccination could be an ideal therapy to reduce the relapse rate.

As a consequence of the pharmacokinetics of active vaccination, it takes at least 4–5 injections with 400 μg NicVAX^®^ before a sufficiently high antibody concentration is acquired. Therefore, smokers who use NicVAX^®^ as smoking cessation therapy may gradually reduce their cigarette consumption before quitting. This process could take up to 16–26 weeks (5^th^ and 6^th^ injection) and could be a disadvantage for smokers who want to quit instantly. This concern may be reduced in the current protocol, which includes a small molecule with a rapid onset of action to allow for early quit attempts, prior to the end of varenicline treatment phase. Another potential shortcoming could be that smokers quit smoking before sufficient antibody titers are achieved and are therefore at increased risk to relapse into smoking. However, varenicline treatment is continued until the point that antibody levels are expected to be adequate. One of the advantages of nicotine vaccination is the increased treatment adherence compared to other cessation therapies due to the mode of administration, and the persistence of antibodies after vaccinations are completed, which may serve a role to maintain abstinence and prevent relapse. Because nicotine-specific antibodies will not interfere within the central nervous system, nicotine vaccination is also likely to have no adverse events related to interference with the central nervous system as in NRTs, antidepressants, and psychotropic medication.

Phase I/II trials assessing the immunogenicity of NicVAX^®^ concluded that continuous abstinence was closely related to the nicotine-specific immune response, in which the top 30% antibody responders had significantly higher abstinence rates than the placebo group. These results confirm the hypothesis that NicVAX^®^ and nicotine-specific antibodies could play a major role in smoking cessation.

Previously published studies on NicVAX^®^ as cessation therapy showed some disappointing results regarding its efficacy on the overall treatment groups. Although NicVAX^®^ was safe and well tolerated, preliminary results on the primary efficacy analysis of two large phase III studies, with a total of 2,000 participants who received 6 injections with 400 μg NicVAX^®^ or placebo, showed that continuous abstinence from week 37–52 was comparable between both treatment groups. At this point there are no published results of the secondary outcome measures of both phase III trials. Despite the disappointing phase III results of NicVAX^®^, we see a potential benefit for nicotine vaccination in future cessation programs, particularly in view of the observation in phase IIb studies that high antibody-responses correlates with increased cessation outcomes. This may be especially relevant if NicVAX^®^ is combined with other cessation aids such as varenicline and counseling.

This phase IIb trial is especially designed as a relapse prevention study, in which smokers who are motivated to quit smoking will be assisted with the use of a 12-week varenicline treatment. The study should allow us to gain more insight in NicVAX^®^ as combination therapy and its efficacy in relapse prevention.

## Appendix A. Secondary objectives

• To evaluate safety and immunogenicity,

• To evaluate long term abstinence from week 37–52,

• A bstinence from week 9–52 and week 37–52 in the subset of NicVAX subjects with the high antibody responses,

• To evaluate four week abstinence from week 9–12,

• To evaluate abstinence from week 37–52 for subjects who were intolerant to varenicline or who were non-abstinent from week 9–12,

• To evaluate point prevalence (7-day abstinence; PP) at 12, 26 and 52 weeks,

• To evaluate relapse rate post week 12 among subjects with 4-week Abstinence status at 12 week. Relapse is defined as at least 2 consecutive weekly diary entries for tobacco use.

• To evaluate abstinence from week 9–24.

• To evaluate time to first Relapse among subjects with 4-week Abstinence status at 12 week,

• To evaluate time to first Lapse among subjects with 4-week Abstinence status at 12 week. Lapse is defined as 1 weekly diary entry for tobacco use followed and preceded by 1 weekly diary entry for tobacco abstinence,

• To evaluate time between first Lapse and first Relapse among subjects with 4-week Abstinence status at 12 week,

• To evaluate withdrawal symptoms using Minnesota Nicotine Withdrawal Scale, measured at screening and during weeks 12–15, weeks 26–29, and weeks 49–52.

• Nicotine dependency measured by the Fagerström Test for Nicotine Dependence.

• To evaluate Cigarette consumption.

## Appendix B. Inclusion and exclusion criteria

### Inclusion criteria

a) Male or female, 18–65 years of age, who has provided written, informed consent, and who, in the opinion of the investigator, is likely to comply with all the requirements of the study.

b) Good general health.

c) Subjects must be smoking an average of at least 10 cigarettes per day during the past year and over the month prior to the screening visit, with no period of abstinence greater than 3 months in the past year.

d) If a female of child-bearing potential: a negative urine pregnancy test, and be willing to use acceptable birth control during study participation (oral, injectable, implantable contraceptive; intrauterine device; or barrier method with spermacide).

e) Alveolar carbon monoxide level ≥ 8 ppm.

### Exclusion criteria

a) Prior exposure to NicVAX^®^ or any other nicotine vaccine.

b) Any known allergic reaction to any components of the vaccine

c) Evidence or history of clinically significant allergic reactions. (Seasonal allergies allowed.)

d) Use of systemic steroids (>10 mg of prednisone or equivalent per day for >14 days), immunosuppressive agents or other medications within 30 days prior to administration of investigational product that might interfere with an immune response, or intention to use such medication within 30 days before or after subsequent investigational product doses. (The use of inhaled steroids is allowed.)

d) Known history of cancer or cancer treatment within 60 months prior to administration of investigational product, except for treated basal cell or squamous cell carcinoma.

e) Known infection with HIV, or congenital or other acquired immunodeficiency.

f) Known history of illicit drug or alcohol abuse or dependence (except nicotine) within 12 months prior to administration of investigational product and for the study duration.

g) Known history of serious psychiatric disorder within 3 months prior to administration of investigational product.

h) Required treatment for depression within the past 12 months.

i) History or current psychosis or bipolar disorder.

j) Current use of antidepressants, antipsychotics, mood stabilizers, naltrexone.

k) Clinically significant cardiovascular disease within the past 6 months. Examples of clinically significant cardiovascular disease would include the following: myocardial infarction, coronary artery bypass graft (CABG), percutaneous transluminal coronary angioplasty (PTCA), unstable angina, serious arrhythmia, or clinically significant ECG conduction abnormalities.

l) Hepatic or renal impairment.

m) Serious or unstable disease within the past 6 months, such as:

Uncontrolled hypertension.

Severe chronic obstructive pulmonary disease.

SGOT (AST) of SGPT (ALT) greater than 150% ULN or total bilirubin greater than 110% ULN.

Elevated serum creatinine.

Other clinically significant laboratory abnormality.

n) Body mass index >38 [calculated as weight (kg)/height^2^ (m)]

o) Known history of any condition or factor judged by the investigator to preclude participation in the study or which might hinder compliance.

p) Use of any smoking cessation treatment, such as over the counter or prescription nicotine replacement therapy (NRT), varenicline, bupropion, clonidine, nortryptyline, mecamylamine within 30 days of the first administration of investigational product, or intention to participate in any other nicotine-related modification strategy outside the scope of this protocol.

q) Intolerance to varenicline.

r) Use of tobacco products other than cigarettes, including pipe tobacco, cigars, snuff, and chew, or marijuana use within the past month and not agreeing to abstain from use of these products during study participation.

s) Use of Botox injections within 30 days prior to administration of investigational product and for the duration of the study.

t) Use of any investigational vaccine 30 days prior to each administration of study product (licensed vaccines may be administered at any time with the exception of one week prior to and one week after administration of investigational product).

u) Previous serious or unexpected adverse reaction to a vaccine, including Guillain-Barré syndrome.

v) Anticipated inability to fulfill all visits and examination procedures throughout the study period (approximately 54 weeks).

w) Receipt of an Investigational New Drug/Device 30 days prior to (or 5 half-lives, whichever is longer) administration of investigational product and for the duration of the study.

